##### Self-Monitoring

During the 28-day intervention period, daily self-monitoring on the basis of AAs will be conducted. The research methodology of AA is well suited to study people in their natural environment, resulting in ecologically valid data from the persons’ everyday life (44). The self-monitoring protocol should detect and monitor micro-processes of mental health and intra-individual variability, as well as the contextual factors in daily life. We aimed to design a brief, but comprehensive protocol for daily self-monitoring of mental health based on self-reports, while attempting to keep participant burden low. The most common areas of psychopathology will be included: Mood, depression, anxiety, stress, sleep, and functional impairment. In addition, physical activity, social activity, daily hassles and daily uplifts, and alcohol and drug use will be monitored as risk and protective factors of mental health. With a total length of 23 items, participants will be able to complete a daily report in under 5 min. All AAs will be time and date stamped.

*Mood*: To self-monitor daily mood, we will use the version of the Multidimensional Mood State Questionnaire (MDBF) from Wilhelm and Schoebi (45). The MDBF was designed specifically for daily life studies with repeated mood ratings, where a parsimonious measure that is sensitive for change is needed. It uses six items to assess the three factors calmness, valence, and energetic arousal in the present moment. Responses are indicated on three separate six-point bipolar scales with the endpoints labeled “very” (“good–bad,” “awake–tired,” and “calm–nervous”).

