#### Primary Outcome

*Mental health*: we will use the extent of psychological distress as a measure of mental health. Psychological distress relates to unspecific behavioral, emotional, cognitive, and psychophysiological components of mental health. The Kessler K6 screening scale will be used (33). The K6 has been extensively used in the World Mental Health Survey and has been validated and translated to German. It consists of six items for the measurement of distress during the past 30 days, resulting in a total score ranging between 0 and 24 points. K6 respondents can be classified into three severity groups, with 0–4 points indicating no distress, 4–12 points moderate distress, and 13–24 points high distress (32).

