*Daily life data*: we will compute Cox proportional hazards models to investigate daily life behavior as risk and protective factors of mental health. Cox proportional hazards models are a type of survival model that allows for the estimation of the hazard (or risk) of an event of interest given prognostic variables. We will model changes in mental health as measured by K6 as the outcome event (i.e., improved, maintained, and deteriorated), and separate models will be computed for well-being, intentions to seek help, and help-seeking behavior as outcome event. As risk and protective factors, we will include daily life measures. Risk factors include alcohol and substance use, the frequency of daily hassles, low social activity, and low physical activity. Protective factors include coping behavior, social support, and physical activity. Furthermore, the instability or variability of daily symptoms over the 30-day monitoring period will also be examined as a risk factor by computing within-person variances, first-order autocorrelation, the mean square successive differences, and the probability of acute change according to Jahng et al. (109). Discrimination ability (the ability of the model to separate individuals who develop the event from those who do not) will be assessed with the C statistic. Model calibration, that measure how accurately model predictions match overall observed event rates, will be evaluated with a version of the goodness of fit (110). Internal model validation will be carried out. For all daily life analysis, data from the AA group will be used (*N* = 62).

*Access*: we will describe access to the intervention in terms of population characteristics (sample representativeness), demographics, clinical characteristics, and sample comorbidities using the appropriate descriptive statistics.

*Engagement*: to assess participant engagement, we will examine the proportion of study drop-outs and the proportion of enrolled individuals who respond to the outcome assessments at each time point, and the proportion of daily life assessments filled out during the 30-day interval.

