The study has implications for vulnerability-stress models. Vulnerability-stress models seek to explain the onset and development of mental ill-health as a combination of predisposed vulnerability together with acute stress from life experiences (116). Such models highlight the role of environmental stressors, who are assumed to trigger the onset of mental disorders among vulnerable persons. Environmental stressors include the lack of social support or meaningful activities. Vulnerability includes, for example, genetic factors, as well as early life experiences that predispose a person to be more susceptible to a mental disorder. A defining characteristic of vulnerability-stress models is the adoption of a dynamic perspective on the development of mental ill-health, including the investigation of causal factors. Researchers who wish to examine this dynamic perspective empirically cannot achieve this with cross-sectional data, but require longitudinal data. In this context, daily life data collected with mobile-based approaches for self-monitoring of mental health can be used to test different hypothesis derived from vulnerability-stress-models.

Analyzing the time course of daily life data from self-monitoring has the advantage, specific hypothesis on the process of development of mental ill-health can be tested. The “Additity hypothesis” within vulnerability-stress models states a straightforward, linear, dose–response relationship between the accumulated effects of stress at a given time and the sum of vulnerability of a person. Thus, the combined effects of stress and vulnerability are assumed to lead to mental disorder. In contrast, the “Ipsative Hypothesis” states an inverse relationship between the two factors. The greater the presence of one factor, the less of the other is needed to facilitate the onset of mental ill-health. As an outcome for vulnerability-stress models, changes in mental health over the 4-week self-monitoring period could be modeled.

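### Two of the four planned instability indices, within-person variance and first-order autocorrelation, also pick up a steady trend in daily symptoms and can carry the size of a K6 change into its own predictor

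*Protocol article*

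**What the plan says.** The daily-life paragraph of Statistical Analysis (Protocol article) states that "the instability or variability of daily symptoms over the 30-day monitoring period will also be examined as a risk factor". The same sentence names the indices: symptom instability "will also be examined as a risk factor by computing within-person variances, first-order autocorrelation, the mean square successive differences" "and the probability of acute change", following a cited method. The outcome is given as follows: "We will model changes in mental health as measured by K6 as the outcome event (i.e., improved, maintained, and deteriorated". Only the self-monitoring-without-support (AA) group is analysed, N = 62.

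Two other sections fix the time frames. On the K6, Primary Outcome says: "It consists of six items for the measurement of distress during the past 30 days". On the daily series, the Self-Monitoring section says: "During the 28-day intervention period, daily self-monitoring on the basis of AAs will be conducted". The daily-life paragraph speaks of 30 days instead; the difference does not matter here.

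Nothing is said for or against removing a trend from the daily series. The person-mean centring described under conditional effectiveness belongs to another analysis, and it removes a person's level, not a slope.

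**The concern.** Variance and lag-1 autocorrelation describe instability only when the series has no systematic drift. If a participant's symptoms fall or rise steadily over the month, both indices go up although day-to-day behaviour is unchanged. A K6 taken at 4 weeks recalls essentially the same month, so a participant with such a drift is also more likely to be classed as improved or deteriorated. Predictor and outcome then share a component.

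Two consequences follow. A report that instability predicts change could reflect nothing more than the change itself. The two indices would also give opposite readings of the same person: higher variance suggests more variability, while higher autocorrelation suggests more inertia. Adjusting for a person's mean symptom level would not help, because a slope is not a level.

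**Working it through.** **The plan's own figure.** 186 participants / 3 groups = 62 in the AA group, as stated. The article gives no figure on trend or instability.

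**Inputs.** From the article: n = 28 daily reports, N = 62, K6 recall of 30 days, and PHQ-2 scored 0 to 6 as an example of a daily scale. Not in the article, hence assumed: day-to-day SD s, true lag-1 correlation rho, and total linear drift D over the 28 days.

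**Step 1, variance.** With slope b = D/27, a linear trend adds b² × n(n+1)/12 = D² × (28 × 29)/(12 × 27²) = 0.0928 × D² to the sample variance. For s = 1:
- D = 1: 1.00 becomes 1.093 (+9%)
- D = 2: 1.00 becomes 1.371 (+37%)
- D = 3: 1.00 becomes 1.835 (+84%)

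Over s = 1.0 to 1.5 and D = 1 to 4 the rise runs from 4% to 149%.

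**Step 2, mean square successive difference.** Without trend it is 2s²(1 − rho); a trend adds only b² = D²/729. For s = 1, rho = 0.3, D = 2: 1.400 becomes 1.4055 (+0.39%). Over the same grid the rise is 0.03% to 1.6%.

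**Step 3, autocorrelation.** For 28 white-noise values the average sample lag-1 autocorrelation is about −0.04. With D = 1 / 2 / 3 SD it becomes 0.04 / 0.21 / 0.38.

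**Step 4, link with change.** Simulation of 62 people over 28 days with rho = 0.3, day-to-day SD varying between people independently of drift, and drift SD 1 / 2 / 3. Mean correlation of each raw index with absolute change:
- variance: 0.15 / 0.47 / 0.71
- autocorrelation: 0.30 / 0.57 / 0.68
- mean square successive difference: 0.01 throughout
- probability of acute change: 0.00 / 0.01 / 0.01

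After linear detrending all are about 0. The correlation with signed change is about 0 for every index, raw or detrended. With scores rounded and cut to 0-6, the raw variance and autocorrelation behave alike (0.13 / 0.49 / 0.74 and 0.29 / 0.58 / 0.70).

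**Step 5, false positives.** Changed and maintained participants were compared by a 5% two-group test, as a simple stand-in for the planned Cox model, with no true difference in instability.

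*20 drifting against 42 stable participants, drift 1 / 1.5 / 2 SD:*
- Everyone with the same day-to-day SD, white noise: variance 21 / 71 / 99%, autocorrelation 32 / 85 / 100%.
- SD varying between people (log-SD 0.3), rho = 0.3: variance 9 / 25 / 53%, autocorrelation 23 / 65 / 96%.
- As the previous line, with rho also varying (SD 0.2): variance 8 / 20 / 52%, autocorrelation 14 / 43 / 80%.
- Wider SD spread (log-SD 0.5): variance 6 / 14 / 33%.
- Detrended indices and the mean square successive difference: about 4-7%.

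*K6 change taken as the difference between two monthly means, rho = 0.3, drift SD 1 to 2, unequal day-to-day SDs:* roughly 7-68% for variance and 15-88% for autocorrelation. If the change happens before the window opens, both are about 5%.

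**The case against.** The strongest reply is that the article does not say the series stay undetrended. It cites a method for the indices and a guidance for data preparation, and a full analysis plan could contain the step. That is fair, and a reader who infers that the sponsor has decided against detrending goes further than the text allows. But the article does fix the statistics, their role, the outcome and the sample, and a variance computed as named includes trend. The request for one sentence stands.

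A reader might also infer that the whole instability analysis is circular, or that every steadily changing participant is scored as unstable. The article does not support this. It also plans the mean square successive difference and the probability of acute change, which a steady trend barely moves. A trend pushes autocorrelation towards inertia, so only the variance reads as more unstable. With all four indices reported, an attentive analyst could recognise the pattern. Nor does the direction of change leak, only its size.

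Two further objections reduce the size. Because the K6 recalls 30 days, K6 change is largely a contrast between two monthly levels, so an early step or a change before the window leaves little trend in the series. The highest variance rates also need equal day-to-day SDs, an implausible premise when instability is being studied as something that differs between people.

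The expectation of no significant change in the control groups is a weaker defence. It concerns group averages, whereas this analysis sorts individuals in the AA group into improved, maintained and deteriorated.

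**Conclusion.** The point holds for two of the four indices. Computed as named, within-person variance and first-order autocorrelation can bring the size of a within-window symptom change into a predictor of K6 change, and they then point in opposite directions about stability.

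The algebra in steps 1 and 2 is exact for a linear trend. The error rates rest on assumptions that the article cannot settle: the size of the drifts, how far day-to-day SD differs between people, a K6 outcome that reflects change inside the window, and a two-group test in place of the Cox model. Under drift SDs of 1 to 2 and unequal SDs, the range is roughly 7-68% for variance and 15-88% for autocorrelation against a nominal 5%, with no inflation if the change came earlier.

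Severity is minor. This is a secondary risk-factor analysis in the AA group and touches no treatment comparison.

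**What to change.** In the daily-life paragraph of Statistical Analysis, add one sentence with either of these:
- remove each participant's linear day trend before computing within-person variance and first-order autocorrelation, and enter the fitted slope as a separate predictor; or
- name the mean square successive difference and the probability of acute change as the main instability indices, with the other two as descriptive.

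The cost is one regression per series and one degree of freedom per participant. Some slow but genuine fluctuation is removed with the trend, and linear detrending only partly removes a non-linear one. The trial was still in preparation when the article was written, so the sentence can be settled before data exist.

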### Trial Status

The trial is in preparation and recruitment will commence after funding has been obtained, approximately in 2018.

## Anticipated Results

This fully mobile RCT will evaluate supportive mental health self-monitoring among smartphone users with psychological distress. Users with moderate to high distress will be oversampled to include all degrees of mental health problems. It compares the intervention toward AAs (self-monitoring without feedback) and a passive control group (no self-monitoring and no intervention). We hypothesize that using the intervention will improve mental health as compared to the control groups, where we expect no significant changes. We will not only test the general effectiveness of the intervention, but also its differential effectiveness (i.e., person-level moderators) and its conditional effectiveness (i.e., time-varying moderators). As the potential risks of using mHealth interventions have not been studied sufficiently, the study will also examine the safety of supportive mental health self-monitoring in regard to detrimental effects on mental health after or during using the application. Finally, the study will provide short-term evidence directly after using the app as well as the long-term sustainability of changes in mental health outcomes. Following current recommendations for evaluating mHealth interventions (100, 101), this study will result in high-quality evidence, allowing for a complete and transparent evaluation of supported self-monitoring on the basis of a smartphone application.

From an epidemiological viewpoint, this study will add important insights into the early development of mental disorders. The existing epidemiological mental health surveys provide good estimates of incidence, prevalence rates, and correlates of mental disorders (111, 112). However, due to their retrospective design, these surveys are limited to a “snapshot” of psychopathology and its correlates. It was found that the time intervals between assessment waves are so long, that there are potentially serious flaws concerning the recall bias (13). Daily life data, as collected during self-monitoring, opens new perspectives for psychiatric epidemiology by capturing the dynamic nature of psychopathology in real-world contexts. Thus, it minimizes the problem of recall bias and maximizes likewise the ecological validity (113). This is especially relevant, considering that mental disorders below clinical thresholds are responsible for a considerable share of the total burden of mental disorders (114), even for more rare mental disorders like psychotic disorders (115). Thus, self-monitoring has the advantage that it is not merely a psychological intervention, but also provides detailed information on the development of mental health over time, related behavior, and the situational context. This information will be used in the proposed study for a comprehensive analysis on risk and protective factors of mental health in daily life.

## Discussion

Despite the substantial burden of mental ill-health on the individual and the economy, there is a significant amount of unmet treatment need in the population. Only about 25% of persons with mental health problems currently receive adequate professional help. To address this treatment gap in mental health care, broadly accessible and evidence-based interventions to monitor and support mental health in daily life are needed. Recently, the use of mHealth technology to improve access to psychological treatment has been suggested. Supportive self-monitoring of mental health in daily life could be a particularly promising mHealth approach. However, additional research is needed to establish supportive self-monitoring as a clinical tool to improve population health in the future.

This study aims to develop and evaluate the first mHealth intervention for mental health on the basis of supportive self-monitoring in the general population. This project will benefit from several lessons learned during previous pilot testing of a smartphone application for mental health self-monitoring (39). The pilot test indicated that mental health self-monitoring is feasible even over longer time periods, if self-monitoring is designed toward minimal participant burden. Pilot testing showed that due to the widespread availability of smartphones in the population, the proposed project does not need proprietary devices to deliver the intervention, rather, the intervention will be available to download on the user’s own Android device. This enables easy access and low-cost distribution. As reaching the target group of smartphone users with psychological distress will be crucial for the present study, a comprehensive, online- and offline-based recruitment campaign will facilitate inclusion. Additional telephone reminders will minimize drop-out during the trial. Blinded outcome assessments by trained telephone interviewers will be conducted, avoiding confounding bias of the intervention outcomes with self-monitoring data, thus providing high-quality data on intervention effectiveness. Additionally, the present study will use objective usage parameters on interaction and engagement with the app to enhance validity. Overall, the proposed project will not only provide new perspectives for psychiatric epidemiology, it also can contribute substantially to the provision of mental health care in the field of early detection and treatment at low costs.

The study has implications for vulnerability-stress models. Vulnerability-stress models seek to explain the onset and development of mental ill-health as a combination of predisposed vulnerability together with acute stress from life experiences (116). Such models highlight the role of environmental stressors, who are assumed to trigger the onset of mental disorders among vulnerable persons. Environmental stressors include the lack of social support or meaningful activities. Vulnerability includes, for example, genetic factors, as well as early life experiences that predispose a person to be more susceptible to a mental disorder. A defining characteristic of vulnerability-stress models is the adoption of a dynamic perspective on the development of mental ill-health, including the investigation of causal factors. Researchers who wish to examine this dynamic perspective empirically cannot achieve this with cross-sectional data, but require longitudinal data. In this context, daily life data collected with mobile-based approaches for self-monitoring of mental health can be used to test different hypothesis derived from vulnerability-stress-models.

Analyzing the time course of daily life data from self-monitoring has the advantage, specific hypothesis on the process of development of mental ill-health can be tested. The “Additity hypothesis” within vulnerability-stress models states a straightforward, linear, dose–response relationship between the accumulated effects of stress at a given time and the sum of vulnerability of a person. Thus, the combined effects of stress and vulnerability are assumed to lead to mental disorder. In contrast, the “Ipsative Hypothesis” states an inverse relationship between the two factors. The greater the presence of one factor, the less of the other is needed to facilitate the onset of mental ill-health. As an outcome for vulnerability-stress models, changes in mental health over the 4-week self-monitoring period could be modeled.

### Limitations

The proposed study has several limitations. First, short screening scales for mental health will be used (self-reports on the device and assessed by telephone interview), but due to feasibility limitations and to minimize participant burden, no diagnostic interview on mental disorders can be conducted (e.g., according to DSM-V).

Second, as participants will self-select themselves into the study, there is potential selection bias. We cannot exclude the possibility that the participants who enroll in the study have certain characteristics that differentiate them from the target group. This means that the generalizability of results is limited to smartphone users who select themselves into using the intervention. However, quota sampling according to age and gender will ensure that the sample will be representative for the population in regard to these characteristics.

Third, potential low response and loss to follow-up present a challenge for this study. Low response/retention rates would reduce the statistical power and can generate a selection bias which affects the generalization of the results. This risk needs to be carefully considered during designing and planning of the study. We will conduct telephone reminders to enhance response. To prevent systematic low response and follow-up loss among hard-to-reach populations, study staff will carefully monitor recruitment rates according to the sample composition in Figure 1: Study flow. Sup-populations showing low response during recruitment will be targeted specifically (e.g., older subjects, male subjects). Using flexible online advertisements, we will place ads that will be shown only to certain sub-populations to enhance response and ensure a representative composition of the sample.

Fourth, potential “gaming” needs to be avoided, which refers to a situation where research participants fraudulently enroll in a study for the purpose of acquiring research payment. Procedures to prevent gaming will include locking the registration procedure in case of participants trying to change submitted answers, availability of study links only for one user/device, and tracking of IP addresses to prevent duplicate enrollment.

Fifth, the event needs to be considered that symptom self-monitoring could have detrimental effects on participants. Appropriate safety measures need to be implemented to counteract participant harm. The study team will consist of a trained staff that can be contacted in the case of a participant experiencing potential detrimental effects. The study team will be available by mail and during telephone hours to provide support, and to forward participants to appropriate mental health-care services.

